### Randomization, allocation, and blinding

2.5

#### Randomisation and allocation

2.5.1

The randomization sequence is generated by an independent third party to ensure unpredictability. A central randomization system is used to prevent investigators from knowing the group assignments in advance. Before the trial commenced, pre-prepared blinded drugs and corresponding emergency letters were allocated to each center in consecutive number segments. Drug dispensing at each center began with the lowest available number, and drugs were sequentially provided to eligible participants based on their enrollment time.

#### Blinding

2.5.2

BBR in the intervention group and placebo in the control group are identical in appearance, packaging and labeling (i.e., same color, shape and odor). Participants are not informed of the actual group assignment. Investigators/assessors are not involved in random allocation, and only record data according to the assigned numbers.

The blinding procedure is supervised throughout by a statistical expert. The implementation of blinding is carried out by staff who are not directly involved in the trial's randomization and drug administration processes. First, the personnel performing the blinding verify the consistency of the appearance and packaging of the study drugs across all groups; subsequently, labels bearing the corresponding drug numbers are affixed to the outer packaging of the respective drug groups. The entire blinding process is documented in detail and securely stored.

The emergency unblinding letters, which contain the group assignment information corresponding to the drug codes, are sealed and distributed to each study center together with the pre-prepared blinded drugs. In an emergency situation, if the investigator deems it necessary to identify the administered drug for the management of an adverse event, unblinding may be performed. The investigator performing the unblinding must document in detail the reason, the date, and his/her signature upon opening the emergency unblinding letter.

Data Monitoring Committee (DMC) independently reviews unblinded data to ensure safety. Unblinding is performed jointly by the independent third party and investigators after study completion or in case of an emergency, to clarify the group allocation.

### Interventions

2.6

Patients will be administered orally at a daily dose of 600 mg (300 mg twice daily, orally), continued for 1 year in the BBR group; and the control group will receive identical-appearing placebo tablets administered at the same dosage regimen (300 mg twice daily) for the same duration. Berberine hydrochloride tablets (0.1 g per tablet) and matching placebo tablets (principal component: starch) were both manufactured and supplied by Chengdu Jinhua Pharmaceutical Co., Ltd.

Conventional Chemotherapy Regimens include the following (23, 24): the single-agent regimen consists of Capecitabine 1,250 mg/m^2^ administered orally twice daily on days 1–14, repeated every 3 weeks; sLV5FU2 involves Leucovorin (LV) 400 mg/m^2^ intravenously over 2 h on day 1, followed by 5-FU 400 mg/m^2^ as an intravenous bolus on day 1, and then 5-FU 1,200 mg/(m^2^·d) via continuous intravenous infusion for 2 days (total 2,400 mg/m^2^ over 46–48 h), repeated every 2 weeks; CAPEOX (also known as XELOX) comprises Oxaliplatin 130 mg/m^2^ intravenously over 2 h on day 1 and Capecitabine 1,000 mg/m^2^ orally twice daily on days 1–14, repeated every 3 weeks; mFOLFOX6 consists of Oxaliplatin 85 mg/m^2^ intravenously over 2 h on day 1, Leucovorin (LV) 400 mg/m^2^ intravenously over 2 h on day 1, 5-FU 400 mg/m^2^ as an intravenous bolus on day 1, and then 5-FU 1,200 mg/(m^2^·d) via continuous intravenous infusion for 2 days (total 2,400 mg/m^2^ over 46–48 h), repeated every 2 weeks; and FOLFOXIRI involves Irinotecan 165 mg/m^2^ intravenously on day 1, Oxaliplatin 85 mg/m^2^ intravenously on day 1, Leucovorin (LV) 400 mg/m^2^ intravenously on day 1, and a total of 2,400–3,200 mg/m^2^ 5-FU via continuous intravenous infusion over 48 h on day 1, repeated every 2 weeks.

### Outcome measures and follow-up

2.7

#### Outcome measures

2.7.1

The primary endpoint is 2-year disease-free survival, defined as the proportion of enrolled patients who develop disease recurrence or death within 2 years following randomization. Recurrence is categorized as either local or distant. Local recurrence is defined as the histologically confirmed reappearance of tumor consistent with the primary lesion at the anastomosis, adjacent bowel, surgical incision, mesentery and lymph nodes, abdominopelvic peritoneum, or retroperitoneum. Distant recurrence refers to metastatic spread of the tumor to distant organs including the liver, lungs, brain, and other extrapelvic sites.

#### Secondary outcome measures

2.7.2

Secondary outcome measures include the 1-year and 2-year recurrence and metastasis rates, as well as the incidence of adverse events. Gut microbiome analysis will be performed using 16S rRNA gene sequencing to compare differences in gut microbial diversity and the abundance of characteristic genera between groups, and metabolomic analysis will be conducted to explore the correlation between serum and fecal metabolic profiles and clinical efficacy.

All assessments will be performed at baseline and every 3 months for 2 years following enrollment, or until disease recurrence or metastasis is observed in participants.

#### Follow-up program

2.7.3

Following the provision of written informed consent, baseline data and biological specimens will be collected from eligible patients in this study. Specifically, demographic data (sex, age), physical examination findings, vital signs, medical history, comorbidities, Healthy Eating Index-2020 (HEI-2020) and tumor characteristics (tumor type, pathological features, metastatic sites, and TNM stage) will be documented via case report forms (CRFs). In addition, routine blood tests, biochemical measurements, tumor marker assays, and imaging examinations will be performed, and clinical biospecimens including blood and fecal samples will be collected.

During the treatment period, regular clinical assessments will be performed, including evaluation of tumor status, occurrence of adverse events, incidence of grade ≥2 diarrhea (Figure 2), chemotherapy dose reductions or delays, and medication adherence. Routine laboratory tests will also be conducted, including complete blood count, biochemical tests, and routine stool examination, as well as imaging examinations consisting of chest-abdomen-pelvis CT or contrast-enhanced abdomen-pelvis CT/MRI. Additionally, if a participant takes any medication other than the chemotherapy agents and the investigational drug, they must report the name, dosage, and duration of treatment to the physician at the follow-up visit. These data will be recorded in the CRF. At the completion of the 1-year treatment period, all participants will undergo standard colonoscopy, and blood and fecal samples will be collected.

**Figure 2 F2:**
[figure not shown]
NCI-CTCAE Diarrhea Grading Scale. This table is based on the National Cancer Institute's (https://dctd.cancer.gov/research/ctep-trials/for-sites/adverse-events) Common Terminology Criteria for Adverse Events (NCI-CTCAE v5.0) (36), the standard classification used in oncology . ADL, activities of daily living. Definition: A disorder characterized by an increase in frequency and/or loose or watery bowel movements. ^a^Instrumental ADL refers to preparing meals, shopping for groceries or clothes, using the telephone, managing money, etc. ^b^Self-care ADL refers to bathing, dressing and undressing, feeding self, using the toilet, taking medications, and not bedridden.

Meanwhile, due to factors such as chemotherapy, subjects may experience grade 2 or higher diarrhea during the study period, so we need to be highly cautious and develop effective treatment plans in advance. When grade 2 or higher diarrhea occurs, emergency medications such as smectite powder, loperamide, or octreotide, should be administered after evaluation by physician. The investigator must record in the CRF detailed information, including the diarrhea grade, name of the rescue medication, dosage, and time of administration. If the patient experiencing Grade 3 diarrhea, the investigational drug will be temporarily discontinued until the toxicity resolves to Grade 1 or baseline, upon which it may be resumed. In addition, once a patient experiencing Grade 4 diarrhea, the investigational drug must be permanently discontinued and the subject discontinue the study.

During the follow-up period, regular assessments of tumor status will be performed, along with routine laboratory examinations including complete blood count, biochemical tests, and routine stool tests, as well as imaging examinations consisting of chest-abdomen-pelvis CT or contrast-enhanced abdomen-pelvis CT/MRI. For each quarterly follow-up visit, a window period of ±7 days is permitted. If a patient is unable to attend the hospital visit, conduct a telephone follow-up and remind the patient to complete the routine check-up. At the end of the 1-year follow-up period, a standard colonoscopy will be performed again, and blood and fecal samples will be collected.

In addition, if disease recurrence or metastasis occurs in the patient during treatment and follow-up, sample collection shall be performed at the time of recurrence and metastasis.

#### Study schedule

2.7.4

The study treatment and assessment plan are summarized in Figure 3.

**Figure 3 F3:**
[figure not shown]
Schedule of enrollment, intervention, and assessments. If the patient experiences recurrence or metastasis within 2 years after enrollment, sample collection should be performed at the time of recurrence or metastasis.

### Data management and monitoring

2.8

We will use the CRF for data collection, which includes general information laboratory examinations, health costs, and so on. Researchers will ensure that the CRFs are filled out accurately and completely. Any incorrect records will be re-filled with the correct information, along with the researcher's signature and date of the day.

A database will be established, encompassing information such as basic patient demographics, diagnosis and treatment details, and imaging assessments. The data of enrolled patients will be reviewed on a regular basis. If any suspicious or discrepant data are identified, the investigator will be contacted for discussion and correction of the data. The database will be locked after the blinded data review report is completed. Quality control-related documents shall be retained, including original records of data consistency checks, range and logic checks, original records generated during the blinded review, and query logs of communications between investigators and monitors.

#### Data monitoring

2.8.1

Monitors will conduct regular follow-up visits in accordance with quality control requirements. Source data will undergo 100% dual review. Any discrepant data must be submitted in a data correction report and will be corrected after review.

### Statistical analysis

2.9

First, normality tests were performed on the measurement data. For data conforming to a normal distribution, parametric statistical methods including *t*-test, paired *t*-test, analysis of variance, and analysis of covariance were used. For non-normally distributed data, nonparametric methods such as rank-sum test and paired rank-sum test were adopted. Enumeration data were analyzed using chi-square test and Fisher's exact test, while ordinal data were analyzed using Ridit analysis, CMH test, or other nonparametric methods. In the multicenter comprehensive efficacy analysis, the CMH test was used for enumeration data, and analysis of covariance was used for measurement data. All statistical analyses were performed using SAS 9.3 software. For patients with missing data due to dropout or loss to follow-up, the last observation carried forward method may be used for imputation, followed by a sensitivity analysis of the results. All statistical tests were two-sided, and P < 0.05 was considered statistically significant.

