## Discussion

3

Postoperative recurrence and distant metastasis remain a formidable clinical challenge in the management of CRC, particularly for patients with advanced-stage disease, in whom recurrence rates are markedly elevated and long-term prognosis is severely compromised. A previous RCT with long-term follow-up demonstrated that BBR may exert a potential preventive effect on colorectal adenoma postoperative recurrence, with its protective effect persisting for up to 6 years or even longer (25). Another study has shown that BBR can exert preventive and therapeutic effects on CRC by binding to SIGMAR1 (26). Building on these prior clinical findings, the present study specifically focuses on patients with stage IIIB and IIIC CRC. Through standardized intervention and long-term follow-up, we aim to further evaluate the preventive efficacy and potential of BBR against postoperative recurrence in this high-risk advanced CRC patient population.

Blood and fecal samples will be collected at baseline, 1-year treatment, 1-year follow-up or upon the occurrence of recurrence and metastasis for multi-omics analyses, specifically metagenomics (16S rRNA sequencing and shotgun metagenomics) and metabolomics (untargeted and targeted approaches). These samples will be used for comprehensive metabolic and mechanistic studies centered on gut microbiota-metabolite interactions and their roles in CRC recurrence.

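### Section 2.9 lets a normality test decide whether baseline is used, so the between-arm genus-abundance comparisons are likely to lose an available adjustment

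*Protocol article*

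**What the plan says.** Section 2.9 (Statistical analysis) opens with a normality test on continuous data. Data that pass go to a list that includes covariance adjustment: "parametric statistical methods including *t*-test, paired *t*-test, analysis of variance, and analysis of covariance were used". For data that fail, the text reads "For non-normally distributed data, nonparametric methods such as rank-sum test and paired rank-sum test were adopted". Further on, for the multicentre efficacy analysis, the same section says "the CMH test was used for enumeration data, and analysis of covariance was used for measurement data". That sentence carries no normality condition and names no covariates. Section 2.9 does not mention the microbiome or metabolomic outcomes by name.

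Section 2.7.2 (Secondary outcome measures) plans 16S sequencing "to compare differences in gut microbial diversity and the abundance of characteristic genera between groups". In the same sentence it gives metabolomics a different purpose: "metabolomic analysis will be conducted to explore the correlation between serum and fecal metabolic profiles and clinical efficacy".

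The baseline paragraph of Section 2.7.3 (Follow-up program) says that "clinical biospecimens including blood and fecal samples will be collected". The Discussion repeats the plan: "Blood and fecal samples will be collected at baseline, 1-year treatment, 1-year follow-up", or when recurrence or metastasis occurs.

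**The concern.** In a randomised comparison of a measure that is also taken before treatment, the baseline value is usually the most useful covariate. Whether to use it should not depend on the shape of the raw outcome, because ANCOVA can be run on a log, centred log-ratio or rank scale.

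Under Section 2.9 as written, the adjusted method is listed for data that pass the normality test, and no adjusted method is named for data that fail. Genus relative abundances are proportions, usually with many zeros and a long right tail, so they can be expected to fail. (This is a general expectation; the article gives no distribution.) Diversity indices may pass or fail, so two microbiome outcomes in the same trial could end up with different estimands and different use of baseline, depending on a preliminary test of the trial data.

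The paired rank-sum test does use baseline, but it asks whether one arm changed and does not compare berberine with placebo.

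At stake is the efficiency of the between-arm microbiome comparisons, which serve the mechanistic secondary objective in Section 2.1. An analyst could also follow either of two unreconciled sentences in Section 2.9.

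**Working it through.** **Step 1. Which outcomes are reached.** The argument needs a between-arm comparison, a baseline value of the same measure, and probable non-normality.

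| Outcome (Section 2.7.2) | Between-arm comparison stated? | Baseline sample? | Reached? |
|---|---|---|---|
| Genus abundance | Yes | Yes (2.7.3, Discussion) | Yes, likely non-normal |
| Microbial diversity | Yes | Yes | Yes, if it fails the test |
| Metabolomics | No: correlation with clinical efficacy | Yes | No |
| 2-year disease-free survival | Yes | Not applicable | No |

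**Step 2. The article's own power figure.** The only one is in Section 2.4, for 2-year disease-free survival: 67% against 77%, two-sided alpha 0.05, power 0.80. With the pooled formula,

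n = [1.960 × √(2 × 0.72 × 0.28) + 0.842 × √(0.67 × 0.33 + 0.77 × 0.23)]² / 0.10² ≈ 316 per arm,

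which agrees with the article. No effect size, standard deviation, power or baseline correlation is given for any microbiome outcome. The 80% reference power and the correlation ρ used below are therefore assumptions, shown over a range.

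**Step 3. Gain from adjustment.** Adjusting for a baseline value with correlation ρ multiplies the residual variance by (1 − ρ²). If the unadjusted test has power P,

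adjusted power = Φ[(1.960 + z_P) / √(1 − ρ²) − 1.960].

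For P = 0.80, z_P = 0.842 and the sum is 2.802. At ρ = 0.5, √(1 − 0.25) = 0.866, 2.802 / 0.866 = 3.235, and Φ(1.275) = 0.899.

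| Assumed ρ | Adjusted power | Gain over 80% (points) |
|---|---|---|
| 0.2 | 81.6% | 1.6 |
| 0.3 | 83.6% | 3.6 |
| 0.4 | 86.4% | 6.4 |
| 0.5 | 89.9% | 9.9 |
| 0.6 | 93.8% | 13.8 |
| 0.7 | 97.5% | 17.5 |

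At ρ = 0.5 with other reference powers, the gain is 11.9 points from 50%, 12.4 from 60%, 11.8 from 70%, 9.9 from 80% and 6.3 from 90%.

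**Step 4. Check with rank methods.** The formula is for a normal model, so the rank-sum test was compared with ANCOVA on ranks by simulation. Each case had 4,000 runs, with normal baseline and follow-up; rank methods give the same result on any monotone scale. The treatment shift was set so that the rank-sum test had about 80% power. The Abstract's total of 306 gives 153 per arm, and Section 2.4 gives 316 per arm before dropout, so both were run.

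| Per arm | ρ | Rank-sum | Rank ANCOVA |
|---|---|---|---|
| 153 | 0.3 | 80.3% | 83.3% |
| 153 | 0.5 | 79.8% | 88.1% |
| 153 | 0.7 | 80.0% | 96.7% |
| 316 | 0.3 | 80.3% | 83.7% |
| 316 | 0.5 | 79.5% | 89.2% |
| 316 | 0.7 | 80.5% | 97.2% |

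The gain at ρ = 0.5 is 8 to 10 points at either size.

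**Step 5. Check with zeros.** With skewed abundances and 20% zeros, rank-sum power was 78 to 80% at 130 per arm (306 less 15%), and rank ANCOVA gave 82%, 88% and 96% at ρ = 0.3, 0.5 and 0.7. At 309 per arm (726 less 15%) it was 79% against 83%, 89% and 97%. Normality was rejected in every replicate. Under no effect, both methods rejected in 4.7 to 5.8% of runs.

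**The case against.** The strongest reply is that Section 2.9 is a short generic paragraph. Its list of nonparametric methods is illustrative, so rank-based ANCOVA may already be allowed. The multicentre sentence also gives ANCOVA to continuous data without any normality condition, and naming covariates is normally left to an analysis plan, which is not shown. This stands in part. A reader might infer that the article binds every non-normal outcome to an unadjusted test, and the text does not support that. What remains is that every method named for non-normal data lacks a baseline-adjusted arm comparison, that the two sentences are not reconciled, and that it is unclear whether the multicentre efficacy analysis covers the microbiome at all.

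A second reply is that the unadjusted test is valid. That is right: the null rejection rates above are near 5% for both methods, and the loss is one of efficiency.

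A third is that the size rests on assumptions. That is also right. A loss of 10 points needs both ρ = 0.5 and 80% reference power. Nothing in the article supports 0.5 for stool samples a year or more apart with adjuvant chemotherapy in between, and at ρ = 0.3 the gain is under 5 points.

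One could also run the rank-sum test on change from baseline. The article does not say so, and it is a weaker remedy. In the same simulation at 153 per arm it had 66.7%, 78.4% and 94.8% power at ρ = 0.3, 0.5 and 0.7, which is worse than no adjustment at 0.3 and no better at 0.5.

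**Conclusion.** The point holds for gut microbial diversity and genus abundance. Section 2.9 ties baseline adjustment to a normality test, names only methods without a baseline-adjusted arm comparison for data that fail it, and contains a second ANCOVA rule that is not reconciled with the first. The stated approach is valid but likely to be less efficient than one the planned samples already allow. At an assumed 80% reference power, the gain forgone runs from about 2 points at ρ = 0.2 to about 18 at ρ = 0.7. These figures are illustrative, because the article gives neither input for these outcomes.

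A reader might extend the point to metabolites. Section 2.7.2 plans metabolomics as a correlation with clinical efficacy and not as an arm comparison, so the power argument does not reach it. A reader might also link it to the biomarker objective in Section 2.1, but that objective concerns prediction of recurrence and not a difference between arms. The primary disease-free survival conclusion is unaffected. This is an inexpensive improvement to secondary, mechanistic analyses.

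**What to change.** In Section 2.9, add a rule for the between-arm microbiome comparisons:

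- Compare arms by ANCOVA on a scale chosen in advance (log or centred log-ratio), or by rank-based ANCOVA where zeros prevent a transformation. Use the baseline value of the same measure and centre as covariates, whatever the normality test shows.
- Report the adjusted between-arm difference with a 95% confidence interval where the transformed scale is used. Rank-based ANCOVA does not directly give a difference in interpretable units, so keep it as the fallback.
- Reconcile the normality rule with the multicentre ANCOVA sentence, and say whether the latter covers the microbiome outcomes.
- Label within-arm paired tests as descriptive.
- Since samples may be taken at recurrence, say which sample such patients contribute to the 1-year and 2-year comparisons.

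The cost is a few lines of text. Baseline samples are already planned, so no patients, visits or specimens are added. The small downside is that the transformation must be chosen before the data are seen.

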## Introduction

1

Colorectal cancer (CRC) represents one of the most prevalent malignant tumors of the digestive tract worldwide and remains a leading cause of cancer-related mortality (1). Recent data from the National Cancer Center (2022) indicate that in China, CRC ranked the second highest incidence among malignant tumors (approximately 10.72%), with a mortality rate ranking fourth (approximately 9.32%), posing a significant public health burden (2). While advances in medical technology have improved early diagnosis and surgical resection rates, postoperative recurrence continues to substantially limit patient survival Clinical evidence shows that approximately 40% of stage III CRC patients experience tumor recurrence and metastasis following radical surgery and standard adjuvant chemotherapy (3). Additionally, the 2-year disease-free survival (DFS) rates demonstrated considerable variation across disease stages: approximately 80% for stage III overall, 79% for stage IIIB, and only 60% for stage III C (4). These findings underscore the urgent need for effect strategies to prevent postoperative CRC recurrence.

Currently, prevention of postoperative recurrence of CRC primarily involves adjuvant antitumor therapy and lifestyle interventions. Evidence suggests that weight management, healthy lifestyle practices, and a diet rich in vegetables, fruits, and whole grains may improve survival outcomes (5). Meanwhile, multiple clinical trials have actively explored therapeutic interventions to reduce recurrence risk-including vitamin D supplementation, postoperative anticoagulation, and nonsteroidal anti-inflammatory drugs (NSAIDs) like aspirin, none have demonstrated their efficacy in large-scale RCTs (6–8). Notably, targeted regulation of gut microbiota has become a research hotspot in the prevention and treatment of CRC progression. Intestinal microbiota dysbiosis appears significantly associated with postoperative recurrence, potentially through mechanisms involving chronic intestinal inflammation secondary to microecological imbalance (9–11).

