#### Inclusion criteria

2.3.2

(1) Patients with pathologically confirmed stage IIIB or IIIC CRC after radical resection, receiving initial treatment;(2) Aged from 18 to 75 years;(3) ECOG performance status score less than 2 (22);(4) Patients who initiate adjuvant chemotherapy within 6 weeks after radical resection of CRC;(5) No local or distant tumor recurrence was determined by imaging;(6) Patients with good communication ability who can comply with the study protocol and complete the study procedures;(7) Patients who have voluntarily signed the informed consent form after fully understanding the study purpose and procedures, disease characteristics, drug effects, related examinations, and potential risks/benefits of this study.

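### Stage IIIB versus IIIC is in neither the stated analysis nor the described allocation; prespecifying it as a CMH stratum with centre would gain a little precision at almost no cost

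*Protocol article*

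**What the plan says.** Section 2.7.1 makes the primary endpoint binary: "The primary endpoint is 2-year disease-free survival, defined as the proportion of enrolled patients who develop disease recurrence or death within 2 years following randomization". Under section 2.9 it is therefore count data, for which two sets of methods are listed. The general one is "Enumeration data were analyzed using chi-square test and Fisher's exact test". The other is for pooling over sites: "In the multicenter comprehensive efficacy analysis, the CMH test was used for enumeration data". No CMH strata are named, and the primary endpoint is not tied to either method by name.

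On stage, the article gives three facts:

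- Section 2.3.2 admits two substages and no others: "Patients with pathologically confirmed stage IIIB or IIIC CRC after radical resection, receiving initial treatment". No mix or cap is given.
- The Introduction gives their 2-year DFS as "79% for stage IIIB, and only 60% for stage III C".
- Section 2.7.3 lists the baseline data, including "tumor characteristics (tumor type, pathological features, metastatic sites, and TNM stage) will be documented via case report forms (CRFs").

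On allocation, section 2.5.1 says that "pre-prepared blinded drugs and corresponding emergency letters were allocated to each center in consecutive number segments". Packs are then dispensed from the lowest number upwards, in order of enrolment. No layer for stage is described.

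**The concern.** By the article's own figures, stage splits the whole trial population into two groups whose 2-year DFS differs by 79% − 60% = 19 points. That is almost twice the 10-point effect (67% versus 77%) for which section 2.4 sizes the trial. The article reports no comparable evidence that centres differ, yet centre is the only factor its stratified test hints at.

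As described, the allocation does not balance stage within centres, so the analysis is where stage can be dealt with. Two things are at stake. One is a small amount of precision, available from a variable that is collected anyway. The other is credibility: if the arms differ visibly in their IIIC share, a borderline result is open to challenge, and an adjustment added afterwards will look chosen from the data.

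**Working it through.** **Inputs.** From section 2.4: 67% versus 77%, two-sided α = 0.05, power 0.80, 1:1, 316 evaluable patients per arm. From the Introduction: 79% (IIIB) and 60% (IIIC). From the Abstract: 306 patients, or 153 per arm, which differs from the 726 of section 2.4; both sizes are shown. Assumed: the IIIB share w, which the article does not give.

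**Step 1. Reproduce the planned size.** With pooled variance under the null and mean rate 0.72:

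n = [1.96·√(2·0.72·0.28) + 0.8416·√(0.67·0.33 + 0.77·0.23)]² / 0.10² = (1.2445 + 0.5311)² / 0.01 = 315.3, so 316 per arm.

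This matches the article. Power at 316 is 80.1%.

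**Step 2. A mix consistent with the plan.** The share at which the two stage rates average to 67% is w = (0.67 − 0.60)/(0.79 − 0.60) = 0.368. This is the base case; 20% to 70% is the range.

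**Step 3. Variance explained by stage.**

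w(1 − w)·0.19² / [p(1 − p)] = 0.2327·0.0361 / (0.67·0.33) = 0.0084/0.2211 = 3.8%.

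On 632 evaluable patients, 3.8% is worth about 24 patients.

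**Step 4. Effect of a chance imbalance.** With stage unstratified, the SD of the between-arm difference in IIIB share is √(2w(1 − w)/n).

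- At 316 per arm: √(2·0.2327/316) = 0.0384. Times 19 points this is 0.73 points, and times 1.96 it is ±1.4 points.
- At 153 per arm: 0.0552, which gives 1.05 points and ±2.1 points.

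At 316 per arm the 95% figure is ±1.2 points for w = 20% and ±1.5 points for w = 50%. For scale, the standard error of the whole DFS difference at 316 per arm is √(0.3982/316) = 3.55 points, so its 95% margin is ±7.0 points. The stage component is (0.73/3.55)² = 4% of that variance.

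**Step 5. Power with and without stage as a stratum.** This used 200,000 simulated trials per setting, with stage left to chance at randomisation. It compared an unstratified chi-square test with a CMH test stratified by stage, without continuity correction. No centre effect was simulated. The common odds ratio that takes 67% to 77% in the base case is 1.68.

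| Per arm | IIIB share (assumed) | Treatment effect | Variance explained | Unstratified | Stage-stratified |
|---|---|---|---|---|---|
| 316 | 36.8% | odds ratio 1.68 | 3.8% | 80.1% | 81.3% |
| 316 | 36.8% | 10 points in each stage | 3.8% | 80.2% | 81.9% |
| 316 | 20% | odds ratio 1.68 | 2.5% | 83.4% | 84.1% |
| 316 | 50% | odds ratio 1.68 | 4.3% | 77.7% | 79.2% |
| 316 | 70% | odds ratio 1.68 | 3.9% | 73.9% | 75.4% |
| 153 | 36.8% | odds ratio 1.68 | 3.8% | 49.5% | 50.8% |
| 153 | 36.8% | 10 points in each stage | 3.8% | 49.5% | 51.1% |

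At 316 per arm the gain is 0.7 to 1.7 points. With no treatment effect, the rejection rate is 0.049 unstratified and 0.050 stratified.

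**The case against.** The strongest reply is that nothing stated here is wrong. A reader might infer that the primary test is stratified by centre alone and deliberately leaves stage out. The article does not say so: section 2.9 names no strata, and it also lists unstratified tests for the same kind of data. CMH strata are often fixed in the analysis plan, which is not shown and may name stage. That part of the reply stands, so the point is a recommendation and does not correct an error.

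A reader might also infer that chance imbalance in stage biases the comparison. It does not. Under randomisation the imbalance is already part of the sampling variance that the unadjusted test allows for, and the simulated type I error confirms this. The ±1.4 points is the edge of a 95% range and lies inside an overall margin of ±7.0 points. The larger ±2.1 points belongs to the Abstract's 306 patients, not to the size derived in section 2.4.

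Finally, the gain is small, and an unadjusted or centre-stratified primary test is a legitimate choice. That also stands. It does not remove the case for the change: each method that the article names, as it is written, leaves a known 19-point prognostic factor unused, and using it costs almost nothing.

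**Conclusion.** The point holds as a low-cost improvement. Stage is absent from the stated analysis and from the described allocation, although the article itself shows it to be strongly prognostic and collects it at baseline. The consequence is forgone precision of about 4% of outcome variance, or about 1 to 2 points of power at 316 per arm, together with avoidable exposure to dispute if the arms happen to differ in stage. Validity and type I error are not in question.

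The sizes rest on the article's 79% and 60% holding in this population, on an assumed IIIB share of 20% to 70%, and on an effect that is constant across stages on the odds or the difference scale. The conclusion is much the same across that range.

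**What to change.** Before unblinding, state in section 2.9 or the analysis plan that the primary 2-year DFS comparison is a CMH test stratified by centre and by stage (IIIB versus IIIC), and that the stage-adjusted difference in 2-year DFS will be reported with its confidence interval. If the analysis plan already says this, cite it.

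The cost is a sentence or two. The variable is already on the case report form, and randomisation and drug numbering need not change. No Cox or other time-to-event model is presumed. Four centres by two stages makes eight strata, on average 632/8 = 79 evaluable patients each, or 306/8 = 38 at the Abstract's size. The article gives neither recruitment by centre nor the stage mix, so the plan should also say how strata will be combined if some turn out very small. Section 3.1 reports that recruitment is under way and gives December 31, 2028 as the expected end, so there is still time to prespecify this.
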